## Quantitative study

### Design

- observational,

- national and multi-center, and

- before/after and here/elsewhere: a comparison of patient health indicators before and after the “PHARE-M training” program at “PHARE-M Group” centers versus “Control Group” centers.

### Primary and secondary endpoints

- FEV1%.

- BMI as an absolute value and as a Z-score (standardized normal distribution of the BMI for children under 2 years of age).

For this research in particular, the value selected for these indicators is the only value appearing in the French CF Registry for a given patient and a given year. It will be analyzed by category of patients defined by age, sex, age at diagnosis, and possibly severity of disease expression, treatment, and certain social characteristics (data appearing in the Registry).

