At the end of the process, 1104 patients remained in each of the two paired groups. The Control Group included 20 CFCs. No paired control patients were found for 205 “PHARE-M patients”. As data are collected in the French Cystic Fibrosis Registry for all patients, exposure variables are identical in both groups. Completeness is similar: for FEV1, 20.2% and 24.5% of missing data corresponding to the children below 6 y.o., for whom this measure is not taken, and 0.6% and 3.5% for ZBMI, in the PHARE-M group and the Control group respectively. The two groups had a similar distribution by age (see Fig. 1). However, there remained a significant difference in average age at diagnosis (PHARE-M paired group: 1.9 years; control paired group: 2.5 years; *p* value: 0.0123); this could be due to the fact that newborn screening was implemented in the 1990s in Brittany, and that seven (out of the 14) CFCs in the PHARE-M Group are located in this region. Furthermore, a significant difference in FEV1% of +3.89% (*p* value = 0.0012) remained in favor of the PHARE-M patient group before the intervention (see Tables 2 and 3).

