### Analysis of the primary endpoint between the two groups

Changes over 5 years in patient health indicators are measured for 2011 (baseline), 2012, 2013, 2014, and 2015; each patient served as his or her own control. A difference in the rate of decline is expected between the two population groups, PHARE-M and control (see Fig. 2). Changes over time in FEV1% will be modeled and compared in the two groups using a mixed model for repeated data with adjustments for potential confounding variables. Measurements for a subject *i* at time *j* is given by the following model, where *ε*_*ij*_ are the normally distributed residual components with mean zero and covariance structure Σ:

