**Fig. 2 Fig2:**
[figure not shown]
Representations of the analysis of the primary endpoint

$$ {Y}_{ij}={\beta}_0^P+{\beta}_1^P{t}_{ij}+{\varepsilon}_{ij} $$ for the PHARE-M group.

$$ {Y}_{ij}={\beta}_0^C+{\beta}_1^C{t}_{ij}+{\varepsilon}_{ij} $$ for the CONTROL group$$ \mathit{\operatorname{cov}}\left({\varepsilon}_{ij},{\varepsilon}_{ik}\right)={\sigma}_{jk} $$

The covariance structure Σ is given by the *σ*_*jk*_. It allows taking into account correlation between measurements on a same subject. Correlation is assumed to be null between subjects. The choice of a covariance structure will be data driven, but we can expect that the correlation between two measurements will only depend on the time lag between them. The most realistic covariance structure should be the so-called Toeplitz covariance matrix. A special case of the Toeplitz model is the first-order autoregressive model.

The question here is to investigate whether the two slopes are parallel or not, that is to test whether $$ {\beta}_1^P $$ = $$ {\beta}_1^C $$ (*H*_0_) versus $$ {\beta}_1^P $$ ≠ $$ {\beta}_1^C $$ (*H*_1_).

Using this model, the slopes (i.e. decline in FEV1) in the two groups will be calculated and compared. Changes over time in BMI will likewise be analyzed by comparing the changes in the two groups from 2011 to 2015, taking into account the Z-score for children under 2 years of age. The average trends will be calculated and analyzed for different patient categories (such as age, sex, age at diagnosis, severity of disease expression, treatment, and certain social characteristics in the Registry). The changes over time in indicators will be presented for the “PHARE-M Group” population by CFC for crossing with the results of the qualitative study.

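### The text ties the BMI Z-score to children under 2 years, but Table 2 reports it for 97.9% of the paired cohort, so the variable for the BMI slope is unclear

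*Protocol article*

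**What the plan says.** The protocol article, under Primary and secondary endpoints, lists FEV1% and then "BMI as an absolute value and as a Z-score (standardized normal distribution of the BMI for children under 2 years of age". Under Analysis of the primary endpoint between the two groups, BMI is to be handled in the same way as FEV1%, by comparing the two groups' changes from 2011 to 2015, "taking into account the Z-score for children under 2 years of age". Both places attach the Z-score to the same age group, and neither mentions a Z-score for older children or adults.

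The section on pairing gives a different picture. After pairing, "1104 patients remained in each of the two paired groups", and missing data are given as "0.6% and 3.5% for ZBMI, in the PHARE-M group and the Control group respectively". Table 2 prints ZBMI means, standard deviations and a test for the whole paired cohort, with 7 and 39 values missing.

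The analysis section also plans trends by patient category, including age. For the PHARE-M group it plans trends by center, to be crossed with the qualitative results. The section on analysis of the questionnaire then looks for a set of factors associated with the largest or smallest impact.

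**The concern.** The endpoint definition and the analysis rule say one thing about which patients have a BMI Z-score, and the baseline table says another. The point in dispute is the outcome variable itself, so an analyst following the text and an analyst following the table would fit different models.

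If the text is followed, the BMI slope in patients aged 2–17 rests on absolute BMI. At those ages absolute BMI changes with growth and puberty, whatever the nutritional status. The slope would then carry a growth component whose size depends on the age mix of the patients being summarized. That matters most where no control arm can absorb it: in the center-by-center PHARE-M trends. Centers are pediatric, adult or mixed, so a pediatric center could appear to improve more than an adult one simply because its patients are growing.

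**Working it through.** **1. Reproduce the printed ZBMI completeness.** Inputs: Table 2, 7 and 39 missing of 1104 each.
- PHARE-M: 7/1104 = 0.63%. Control: 39/1104 = 3.53%. Both match the printed 0.6% and 3.5%.
- Available: 1097 + 1065 = 2162 of 2208 = 97.9%.

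**2. How many could have a Z-score under the stated age limit?** Input: Table 2, age class 0–4, 182 + 175 = 357.
- With ages spread evenly within the class, under-2s are 2/5 × 357 ≈ 143, or 6.5% of 2208.
- Even if the whole class were under 2: 357/2208 = 16.2%, so ZBMI would be missing in at least 83.8%.
- Neither figure is compatible with 97.9% available.

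**3. Does the printed test agree?** Inputs: Table 2, means −0.17 and −0.14, SDs 1.05 and 1.15, printed p = 0.5171. Normal test, SE = √(1.05²/n₁ + 1.15²/n₂). Rounding of the means allows a difference of 0.02 to 0.04.

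| Patients with ZBMI | n₁, n₂ | p at 0.03 | p over 0.04 to 0.02 |
|---|---|---|---|
| Nearly all | 1097, 1065 | 0.527 | 0.40–0.67 |
| All aged 0–4 | 182, 175 | 0.80 | 0.73–0.86 |
| Under 2 (interpolated) | 73, 70 | 0.87 | 0.83–0.91 |

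Only the near-complete cohort fits the printed value.

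**4. Can the literal rule give a Z-score slope over 2011–2015?** Outcomes are "measured for 2011 (baseline), 2012, 2013, 2014, and 2015". Cohort members had to be seen at a center in 2012, so all were born by the end of 2012 and all are at least 2 in 2015. No one would have a Z-score in the last year. For 2014 this is not certain, because a child born late in 2012 could be measured before the second birthday.

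**5. Who would be left on absolute BMI while still growing?** Inputs: Table 2 classes 0–4 (357), 5–9 (415), 10–14 (417), 15–19 (337). Ages 2–17 are taken as 3/5 of the first class, all of the middle two, and 3/5 of the last.
- Total: (214.2 + 415 + 417 + 202.2)/2208 = 1248.4/2208 = 56.5%.
- PHARE-M: 632.6/1104 = 57.3%. Control: 615.8/1104 = 55.8%.
- Bounds counting none or all of the two split classes: 832/2208 = 37.7% and 1526/2208 = 69.1%.

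**6. How much growth enters which comparison?** Assumption, not from the document: absolute BMI rises 0.3–0.6 kg/m² per year at ages 2–17 and is flat otherwise.
- Within a group: about 0.57 × 0.3 to 0.57 × 0.6 = 0.17–0.34 kg/m² per year.
- Between groups: (632.6 − 615.8)/1104 = 0.0152; times 0.3–0.6 gives 0.005–0.009 kg/m² per year.
- Between PHARE-M centers, extreme case of all patients aged 2–17 against none: the full 0.3–0.6 kg/m² per year. The document gives no age mix by center, so real differences lie somewhere below this.

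**The case against.** The strongest reply is that the near-complete ZBMI data show the investigators already compute the Z-score at all ages, so the age limit may be a slip of wording or translation. That is possible, but the text cannot show it. The limit is printed in both the definition and the analysis rule, so it needs correcting either way.

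The second reply is that growth common to both groups drops out of a test of slope difference. This largely stands. The article states that "The two groups had a similar distribution by age", Table 2 bears it out, and the model is fitted "using a mixed model for repeated data with adjustments for potential confounding variables". A reader might infer that the BMI analysis could not show a nutritional effect at all. The documents do not support that for the overall contrast, where step 6 leaves less than 0.01 kg/m² per year. What remains there is added variance. The reply does not reach the within-group, age-category or per-center trends.

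A reader might also infer that the youngest children change from Z units to kg/m² partway through a single trend, with a large artificial jump. The analysis wording is compatible with that, but the endpoint list names absolute BMI and the Z-score as two forms, and no section describes one outcome that switches scale. The jump is therefore not established.

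Finally, the limitations section names FEV1% as the primary endpoint, which lowers the weight of BMI. But the abstract puts FEV1 and BMI together in the main comparison, and the audit section counts height and weight among the data behind the primary endpoints. An article may leave the reference standard to a fuller document; that does not excuse a printed rule that its own table contradicts.

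**Conclusion.** The point holds as an internal contradiction about the BMI outcome. The definition and analysis rule tie the Z-score to an age group of at most 16.2% of the paired cohort, while the reported data cover 97.9%, and the printed p-value fits only the latter. These findings rest on figures in the article alone, as does the absence of any Z-score in 2015 under the literal rule.

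The consequence is limited in scope. About 56.5% of patients would be on absolute BMI at growing ages; that share assumes an even spread within five-year classes, and without it the range is 37.7%–69.1%. The growth figures rest on an assumed yearly rise. On that assumption the overall group contrast is barely biased, while within-group, age-category and per-center PHARE-M trends become partly a measure of age mix. The per-center trends matter most, because they feed the search for factors linked to impact.

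**What to change.** Correct Primary and secondary endpoints and Analysis of the primary endpoint between the two groups so that both agree with Table 2:

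- Name the age- and sex-specific BMI Z-score as the variable for the 2011–2015 slope comparison and for the per-center trends. Apply it to all patients for whom it is computed, at minimum everyone under 18, and state the ages covered and the reference used.
- Keep one scale per patient for the whole follow-up, including those who pass an age boundary between 2011 and 2015.
- Report absolute BMI separately, for patients who are adults at baseline.

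The cost is a change of wording in two sections. No new data are needed, since ZBMI is already available for 2162 of 2208 patients at baseline.

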### Study population

A closed cohort was formed to identify the study population including the patients followed up at CFCs who met the following inclusion criteria according to the 2012 Registry data:patients seen at a CFC in 2012patients having two of the CF-causing mutations of the CFTR2 list published on Feb 2012patients not having received a transplant in 2012

A patient left the cohort if he or she no longer met the inclusion criteria after the annual data were updated in the Registry (2013, 2014, and 2015), i.e.: if he or she was a carrier of a mutation excluded from the CFTR2 list updated on 13/08/2015 [1]; if he or she was followed up at a CFC engaged in the PHARE-M in 2014 or 2015; if he or she changed CFC in the course of the study and in doing so, changed CFC group; if he or she received a transplant between 2013 and 2015 (data up to the transplantation were taken into account), or if the patient died between 2013 and 2015 (data up to the death were taken into account).

The cohort was divided into two groups: the “PHARE-M Group” and the “Control Group”:The “PHARE-M Group” consisted of the patients followed up at one of the 14 CFCs trained in the PHARE-M in the experimental phase (1309 patients).The “Control Group” consisted of the patients followed up at the CFCs not having benefitted from the intervention in the same period of time (2490 patients).

### Pairing of the two “PHARE-M” and “control” groups

A preliminary analysis of the cohort formed from the 2012 Registry data showed significant differences between the two groups of patients, before the PHARE-M intervention, in terms of: 1) distribution by age, 2) distribution by age at diagnosis, and 3) distribution by FEV1% value (see Table 1).

**Table 1 Tab1:** Distribution by age, age at diagnosis and FEV1% of the 2012 study population between the two groups of the study cohort before pairing

Comparison of the two groups	PHARE-M (*N* = 1051)			Control (*N* = 1962)		
Comparison of Ages	Avg.	Med.	Max.	Avg.	Med.	Max.
Age of patients (years)	15.0	13.0	62	18.0	17.0	74
Age at diagnosis (years)	2.0	0.1	51	3.2	0.2	71
Comparison of FEV1%	Avg.	LLM	ULM	Avg.	LLM	ULM
FEV1%	83	81,55	84,45	75,48	74,33	76,64

Consequently, a 1:1 pairing of the patients from the Control Group was decided in an attempt to eliminate certain confounding factors that could be attributed to the type and size of the CFC to which the patient was assigned: each “PHARE-M patient” was associated with a “control patient” followed up at a center of the same type (pediatric, adult, or mixed) caring for a total number of patients belonging to the same interval ([1;50], [51;100], [101;150], [151;200], or [> = 200]). Reunion island CFCs were excluded from the Control Group to reduce heterogeneity in CF care. All “eligible” control patients for each patient in the PHARE-M Group were selected, and one control patient was randomly drawn from that group of eligible control patients (without replacement). The patients in the PHARE-M Group were paired in a random order.

At the end of the process, 1104 patients remained in each of the two paired groups. The Control Group included 20 CFCs. No paired control patients were found for 205 “PHARE-M patients”. As data are collected in the French Cystic Fibrosis Registry for all patients, exposure variables are identical in both groups. Completeness is similar: for FEV1, 20.2% and 24.5% of missing data corresponding to the children below 6 y.o., for whom this measure is not taken, and 0.6% and 3.5% for ZBMI, in the PHARE-M group and the Control group respectively. The two groups had a similar distribution by age (see Fig. 1). However, there remained a significant difference in average age at diagnosis (PHARE-M paired group: 1.9 years; control paired group: 2.5 years; *p* value: 0.0123); this could be due to the fact that newborn screening was implemented in the 1990s in Brittany, and that seven (out of the 14) CFCs in the PHARE-M Group are located in this region. Furthermore, a significant difference in FEV1% of +3.89% (*p* value = 0.0012) remained in favor of the PHARE-M patient group before the intervention (see Tables 2 and 3).

**Fig. 1 Fig1:**
[figure not shown]
Distribution by population age between the two groups (PHARE-M and control), paired in 2012 data

**Table 2 Tab2:** Comparison between the PHARE-M Group and the paired Control Group

Comparison between PHARE-M Group and Control Group		PIIARE-M (*N* = l104)	Controles (*N* = 1104)	Patients PHARE non paired (*N* = 205)	Comparison between PIIARE-M Group and Control Group (proc TTEST)
Gender	Men *n (%)*	582 (52.72)	564 (51.09)	93 (45.37)	
	Female *n (%)*	522 (47.28)	540 (48.91)	112 (54.63)	
Age	Average	15.57	16.05	14.48	
	Std Deviation	10.73	11.00	10.51	
Age (classes)	0-04 *n (%)*	182 (16.49)	175 (15.85)	32 (15.611)	
	05-09 *n (%)*	209 (18.93)	206 (18.66)	42 (20.49)	
	10-14 *n (%)*	213 (19.29)	204 (18.48)	48 (23.41)	
	15-19 *n (%)*	169 (15.31)	168 (15.22)	38 (18.54)	
	20-24 *n (%)*	125 (11.32)	130 (11.78)	19 (927)	
	25-29 *n (%)*	93 (8.42)	84 (7.61)	10 (4.88)	
	30-34 *n (%)*	53 (4.80)	68 (6.16)	4 (1.95)	
	35-39 *n (%)*	36 (3.26)	34 (3.08)	6 (2.93)	
	40-44 *n (%)*	7 (0.63)	18 (1.63)	1 (0.49)	
	45-49 *n (%)*	9 (0.82)	11 (1.00)	4 (1.95)	
	50-54 *n (%)*	4 (0.36)	3 (0.27)	0	
	55-59 *n (%)*	4 (0.36)	2 (0.18)	0	
	60-64 *n (%)*	0	0	1 (0.49)	
	70-74 *n (%)*	0	1 (0.09)	0	
VEMS	Nmtss	223	270	49	(*p* = 0.0012 IS)
	Average	83.00	79.11	85 06	
	Std Deviation	23.96	25.81	21.92	
ZBMI	Nmiss	7	39	2	*p* = 0.5171 (NS>)
	Average	-0.17	-0.14	-0.18	
	Std Deviation	1.05	1.15	1.11	

*S* Significant; *NS* Non Significant

**Table 3 Tab3:** Comparison of Age at diagnosis between PHARE-M and Control

Age at diagnosis (years)			
	Control	PHARE-M	Patients PHARE non paired
Nmiss	33	39	2
Average	2.49	1.85	2.47
Std Deviation	6.34	5.33	6.30
Comparison of Age at Diagnosis between PHARE-M and Control Groups		0.1317	*P*-value*

*Test de Wilcoxon

### Analysis of the primary endpoint between the two groups

Changes over 5 years in patient health indicators are measured for 2011 (baseline), 2012, 2013, 2014, and 2015; each patient served as his or her own control. A difference in the rate of decline is expected between the two population groups, PHARE-M and control (see Fig. 2). Changes over time in FEV1% will be modeled and compared in the two groups using a mixed model for repeated data with adjustments for potential confounding variables. Measurements for a subject *i* at time *j* is given by the following model, where *ε*_*ij*_ are the normally distributed residual components with mean zero and covariance structure Σ:

**Fig. 2 Fig2:**
[figure not shown]
Representations of the analysis of the primary endpoint

$$ {Y}_{ij}={\beta}_0^P+{\beta}_1^P{t}_{ij}+{\varepsilon}_{ij} $$ for the PHARE-M group.

$$ {Y}_{ij}={\beta}_0^C+{\beta}_1^C{t}_{ij}+{\varepsilon}_{ij} $$ for the CONTROL group$$ \mathit{\operatorname{cov}}\left({\varepsilon}_{ij},{\varepsilon}_{ik}\right)={\sigma}_{jk} $$

The covariance structure Σ is given by the *σ*_*jk*_. It allows taking into account correlation between measurements on a same subject. Correlation is assumed to be null between subjects. The choice of a covariance structure will be data driven, but we can expect that the correlation between two measurements will only depend on the time lag between them. The most realistic covariance structure should be the so-called Toeplitz covariance matrix. A special case of the Toeplitz model is the first-order autoregressive model.

The question here is to investigate whether the two slopes are parallel or not, that is to test whether $$ {\beta}_1^P $$ = $$ {\beta}_1^C $$ (*H*_0_) versus $$ {\beta}_1^P $$ ≠ $$ {\beta}_1^C $$ (*H*_1_).

Using this model, the slopes (i.e. decline in FEV1) in the two groups will be calculated and compared. Changes over time in BMI will likewise be analyzed by comparing the changes in the two groups from 2011 to 2015, taking into account the Z-score for children under 2 years of age. The average trends will be calculated and analyzed for different patient categories (such as age, sex, age at diagnosis, severity of disease expression, treatment, and certain social characteristics in the Registry). The changes over time in indicators will be presented for the “PHARE-M Group” population by CFC for crossing with the results of the qualitative study.

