## Abstract

**Background:**

The PHARE-M care quality improvement program, modeled on the US Cystic Fibrosis Quality Improvement Program, was introduced at 14 cystic fibrosis centers (CFCs) in the French Cystic Fibrosis Network between 2011 and 2013. The pilot phase assessments attested the progressive adherence of the teams and improvements in care management. The PHARE-M Performance research project aims at assessing in 2015 the impact of the PHARE-M program on patient health indicators at trained versus untrained centers. It also sought to identify contextual factors that could account for variability in the performance of the PHARE-M among the trained centers.

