**Fig. 3 Fig3:**
[figure not shown]
Modeling of the intervention, context, and mechanisms

The PHARE-M intervention consisted of establishing, training and coaching a quality team (QT) at each CFC comprising a number of professionals from the multidisciplinary CF team and 1 parent or patient from the CFC’s caseload. The members of the QT have been trained in quality methods and tools and coached in changing care processes. The PHARE-M intervention should have directly impacted the ability of the local QT to master QI methods and tools, lead changes in the care processes, and should have generated good appreciation of the utility of the QT efforts. This direct impact of PHARE-M is identified under the heading “QT effectiveness”. QT effectiveness may not only be the result of the PHARE-M intervention but may have been modulated by internal mechanisms, such as the composition of the QT (number of members and disciplines enlisted), its functioning (rigor in the QI work, decision-making, clarity of the roles…) and the parent or patient engagement. Those mechanisms are represented as impacting QT effectiveness (Table 3). Beyond the ability to master the QI methods and tools, the PHARE-M intervention was expected to have an impact on the quality of CF care delivered at the CFC. The Chronic Care Model [12] was deemed appropriate to account for quality of CF care across the 6 dimensions: existing improvement goals, multidisciplinary care, self-management support, decision support (use of evidence-based guidelines), use of information system and electronic patient record, and organization of resources in the patient’s community of life. Finally, an indirect impact of the PHARE-M intervention is expected on the trend in patient outcomes’ evolution as measured in the quantitative part of this study. Moreover, some elements in the CFC contexts, which are external to the PHARE-M intervention and preexisted to its introduction, may have had a major impact both on the adherence of the team to the QI work and on its outputs. The contextual elements that have been brought in this study include the composition of the MDT, the leadership, the patient-centeredness of care, the innovative culture of the team, and the support from the hospital quality department.

The qualitative study will test these hypotheses using a questionnaire to be self-administered, in 2015, to all members of the MDT at the 14 CFCs and to the patients/parents participating in the quality teams.

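### The primary slope test treats patients as independent although PHARE-M is delivered to whole centers, so any center-to-center variation in decline makes its standard error too small

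*Protocol article*

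**What the plan says.** The section on the analysis of the primary endpoint says that FEV1% over 2011 to 2015 will be compared "using a mixed model for repeated data with adjustments for potential confounding variables". The model is written out: one intercept and one slope per group, plus a residual with covariance matrix Σ, expected to be Toeplitz or first-order autoregressive. Of Σ the article says "It allows taking into account correlation between measurements on a same subject", and then "Correlation is assumed to be null between subjects". The hypothesis follows directly: "The question here is to investigate whether the two slopes are parallel or not", with a two-sided alternative. BMI is to be analyzed in the same way.

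The intervention consisted of "establishing, training and coaching a quality team (QT) at each CFC" (Qualitative study, Design). Under Study population, membership of a group is decided by the center attended. After pairing there are 1104 patients per group, and "The Control Group included 20 CFCs", against 14 trained centers. The article mentions no center effect, center-specific slope, cluster-robust variance or center-level test. Results by center are foreseen only for the PHARE-M group, to be set against the qualitative findings.

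**The concern.** Exposure does not vary between patients of the same center, so the effective comparison is 14 centers with 20. The model counts 2208 patients as independent units. If average decline differs somewhat between centers for reasons unrelated to PHARE-M, that variation does not average out over patients within a center. It averages out only over centers. The reported standard error omits it, and the reference distribution uses patient-level degrees of freedom.

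The article itself gives reasons to expect such variation:

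- Its second aim is to find "contextual factors that could account for variability in the performance of the PHARE-M among the trained centers", and it plans to relate center-specific trends to center characteristics.
- Under Limitations it reports that the audit of the outcome data found discrepancies arising mainly from how each center read the data-selection rule. It links their volume to a rule change applied from the 2011 survey, which is the baseline year. Uneven uptake across centers could produce apparent trends specific to a center.

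At stake is the headline result. A significant difference in FEV1 decline could be ordinary center variation, and it would inform whether the program is extended to the remaining centers.

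**Working it through.** **Inputs from the article**

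- 14 PHARE-M and 20 control centers; 1104 patients per group after pairing.
- FEV1 missing in 2012 (Table 2): 223 and 270, leaving 1104 − 223 = 881 and 1104 − 270 = 834.
- Mean patients per center: 1104/14 = 78.9 and 1104/20 = 55.2; with FEV1, 881/14 = 62.9 and 834/20 = 41.7.

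Some young children without FEV1 in 2012 will contribute values later, so the two sets of numbers roughly bracket the primary analysis. For the BMI z-score few values are missing (7 and 39, leaving 1097 and 1065), so the 1104 figures are close to that case.

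**Assumptions.** The article gives no slope ICC, and no significance level for this test. I take a two-sided 5% level and define the ICC as the share of the variance of patient slopes that lies between centers. An ICC of 0.01 means a between-center SD of slopes equal to √0.01 = 0.1 of the total SD of patient slopes.

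**Check of inputs.** The article states no standard error or power for the slope test, so there is no such figure to reproduce. Its baseline comparison can be reproduced: 83.00 (SD 23.96, n = 881) against 79.11 (SD 25.81, n = 834) gives t = 3.24 and p = 0.0012, as stated. That test also treats patients as independent.

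**Formulas.** With m₁ = N₁/14 and m₂ = N₂/20,

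Variance inflation DE = {[1 + (m₁ − 1)·ICC]/N₁ + [1 + (m₂ − 1)·ICC]/N₂} / (1/N₁ + 1/N₂)

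True type I error = 2·[1 − Φ(1.96/√DE)]

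**Example, ICC 0.01, 881/834 patients.** The group factors are 1 + 61.9 × 0.01 = 1.62 and 1 + 40.7 × 0.01 = 1.41. Weighting by 1/N gives DE = 1.51 and √DE = 1.23. Type I error = 2·[1 − Φ(1.96/1.23)] = 11.1%.

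| Slope ICC (assumed) | 881/834: DE | SE too small by | Type I error | 1104/1104: DE | SE too small by | Type I error |
|---|---|---|---|---|---|---|
| 0 | 1.00 | 1.00 | 5.0% | 1.00 | 1.00 | 5.0% |
| 0.002 | 1.10 | 1.05 | 6.2% | 1.13 | 1.06 | 6.5% |
| 0.005 | 1.26 | 1.12 | 8.0% | 1.33 | 1.15 | 8.9% |
| 0.01 | 1.51 | 1.23 | 11.1% | 1.66 | 1.29 | 12.8% |
| 0.02 | 2.02 | 1.42 | 16.8% | 2.32 | 1.52 | 19.8% |
| 0.05 | 3.55 | 1.88 | 29.8% | 4.30 | 2.07 | 34.5% |
| 0.10 | 6.10 | 2.47 | 42.7% | 7.60 | 2.76 | 47.7% |

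**Simulation.** The formula assumes equal center sizes within each group. A simulation with no true effect, 881 and 834 patients spread unequally over 14 and 20 centers, and 4000 runs per ICC gave these rejection rates:

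| Slope ICC | Patient-level test | t-test on 34 center slopes |
|---|---|---|
| 0 | 5.1% | 4.3% |
| 0.005 | 9.1% | 4.0% |
| 0.01 | 12.3% | 4.2% |
| 0.02 | 19.3% | 5.0% |
| 0.05 | 33.2% | 4.4% |
| 0.10 | 48.0% | 4.8% |

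Unequal center sizes add to the inflation, and a center-level test holds the nominal level throughout.

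**The case against.** The best counter-argument is that the harm is conditional. The inflation exists only if slopes cluster by center, and the article gives no figure for that. Center differences in FEV1 level would largely cancel in a comparison of slopes. At an ICC of 0.002 the error rate is only 6.2%. French CF care follows a national protocol with full reimbursement, the Reunion centers were excluded to limit heterogeneity, and pairing was on center type and size. All of this points to a smaller center variance.

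This stands as a caution about size. It does not support fixing the correlation at zero. Pairing on type and size class leaves correlation among patients of the same center, separate group intercepts deal only with the difference in baseline means, and fixed covariates do not remove residual center-by-time variance. The point about levels does shape the remedy: a random center intercept alone would not be enough.

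Two supporting arguments should not be pressed. The second aim concerns variation in program impact among trained centers, so it is in tension with the zero-correlation assumption but does not strictly contradict it. The survival gap cited in the Background comes from an unpublished US benchmark of the ten best centers against the rest, and it says little about FEV1 slopes in France.

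The article does concede that centers volunteered and that causal attribution may be difficult. That tempers interpretation but does not correct a standard error. Nor can the matter be left to an unseen analysis plan, because the article makes the choice explicitly.

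**Conclusion.** The concern holds, and the primary model should be changed before analysis. The stated assumption of no correlation between patients does not fit an exposure delivered to centers. For any positive within-center correlation of slopes the error goes one way: the standard error is too small and the false-positive rate is above nominal. Over an assumed ICC of 0.005 to 0.05, a nominal 5% test rejects in 8.0% to 29.8% of null cases (881/834 patients) or 8.9% to 34.5% (1104 per group). An ICC of 0.01 already more than doubles the nominal rate. The exact size depends on an ICC that the article does not give, and at an ICC of zero there is no inflation. The figures also assume that all 14 PHARE-M centers still contribute after 205 of their patients went unpaired, which the text does not confirm; fewer centers would make matters worse. The BMI analysis has the same fault.

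**What to change.** Replace the zero-correlation sentence with a three-level specification for FEV1% and BMI: a center-level random intercept and a center-level random time slope, in addition to the within-patient covariance. Test the slope difference with Kenward-Roger or Satterthwaite degrees of freedom, about 34 − 2 = 32. As a check, report a comparison of the 34 adjusted center slopes. Cluster-robust inference with a small-sample correction would be an acceptable alternative.

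Add a rule for assigning patients to centers. Under Study population, a patient who changes center leaves the cohort only if the move also changes group, so some patients will be seen at two centers of the same group. Assigning each patient to the center attended in 2012, the year that defines the cohort, would settle this.

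The cost is one additional random-effects statement, the assignment rule and some plan wording. No new data are needed. Confidence intervals will widen by roughly the factors in the table (1.23 at an ICC of 0.01 with 881/834 patients), which reflects what 34 centers can support. The change does not address confounding from the centers having volunteered.
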